# Efficacy of denervation for osteoarthritis in the proximal interphalangeal joint (DOP): protocol of a randomized controlled trial

**DOI:** 10.1186/s13063-024-08399-w

**Published:** 2024-08-22

**Keywords:** Osteoarthritis, Proximal interphalangeal joint, Exercise therapy, Patient education, Denervation, Randomized controlled trial

## Abstract

**Background:**

Osteoarthritis (OA) contributes increasingly to disability worldwide. There is ample high-quality research on the treatment of knee and hip OA, whereas research on surgical and non-surgical treatment in hand OA is sparse. Limited evidence suggests that education and exercise may improve pain, function, stiffness, and grip strength in hand OA. The established surgical options in hand OA have disadvantages. Prostheses preserve motion but have a high complication rate, whereas fusions decrease function due to limited movement. There is an unmet need for high-quality research on treatment options for hand OA and a need for the development of effective and safe movement-sparing therapies.

This study aims to compare the effects of a motion-preserving surgical treatment (denervation of the proximal interphalangeal (PIP) joint) with a patient education and exercise program on patient-reported outcomes and objective function in painful PIP OA.

**Methods:**

In this parallel-group, two-armed, randomized, controlled superiority trial (RCT), 90 participants are assigned to surgical PIP joint denervation or education and exercise. Pain on load 1 year after intervention is the primary outcome measure. Secondary outcome measures include pain at rest, Patient-Rated Wrist and Hand Evaluation (PRWHE), HQ8 score, EQ5D-5L, objective physical function, complications, two-point discrimination, Mini Sollerman, consumption of analgesics, and the need for further surgery. Assessments are performed at baseline, 3 and 6 months, and 1 year after intervention.

**Discussion:**

There are no previous RCTs comparing surgical and non-surgical treatment in PIP OA. If patient education plus exercise or PIP denervation improve function, these treatments could be implemented as first-line treatment options in PIP OA. However, if denervation does not achieve better results than non-surgical treatment, it is not justified to use in PIP OA.

**Trial registration:**

Prospectively registered in ClinicalTrials.gov (NCT05980793) on 8 August 2023. URL https://classic.clinicaltrials.gov/ct2/show/NCT05980793.

**Supplementary Information:**

The online version contains supplementary material available at 10.1186/s13063-024-08399-w.

## Background

Osteoarthritis (OA) in the finger joints is very common, especially from middle age and in women, and may cause significant disability. The prevalence of symptomatic hand OA is 26% in women over 70 years of age, with an estimated lifetime risk of OA of 47% among women as compared to 25% in men [1, 2].

Common surgical options for proximal interphalangeal (PIP) joint OA are arthroplasty or arthrodesis. Arthroplasty preserves some motion [3] but has a reported complication rate of 35% 2 years postoperatively [4] and with a complication rate considerably higher than for arthrodesis [3]. A successful fusion is achieved for PIP joint arthrodesis in 95–97% of cases [5, 6] but results in impaired function due to loss of movement. Considering the disadvantages of previously described surgical treatments, there is an unmet need for effective and safe movement-sparing therapies for PIP joint OA.

Surgical joint denervation is a motion-sparing intervention, where sensory articular branches to the joint are sectioned. It has predominately been used in wrist OA, with reported high participant satisfaction, increased grip strength, and improved average pain scores [7]. Case series of PIP joint denervation in 11–54 joints have reported improved pain VAS (0-10) scores of 6–6.4 units [8–10] and an increase in range of motion of 10–25° [8, 9]. A recent systematic review of PIP joint denervation performed through a palmar approach reported 90% participant satisfaction; however, complications were observed in 14%, mainly with transient paresthesia [11]. Hence, there are low-quality evidence of encouraging results after PIP joint denervation, but to our knowledge, there are no randomized controlled studies of PIP joint denervation compared to other types of treatment.

Conservative treatment of finger joint OA includes patient education, exercise, splints, analgesics, or intraarticular glucocorticoid injections. Although patient education and exercise are considered the standard first-line treatments in hip and knee and OA [12], research regarding the effectiveness of these interventions in hand OA is limited. Reports suggest that hand exercise may improve pain and function, joint stiffness, and grip strength [13] and that education and training in ergonomic principles and joint protection also may be effective [14].

## Objective

The objective of this study is to evaluate the effects of PIP denervation compared with a nonsurgical treatment patient education and exercise on pain at rest and on load, hand function, quality of life, range of motion, and strength in patients with painful PIP joint OA.

We hypothesize that denervation will decrease pain and improve objective function more effectively than patient education plus exercise for OA in the PIP joint.

## Methods and analysis

### Study design

The study is designed as a parallel group, two-arm, prospectively registered randomized, controlled superiority trial. Data analysts are blinded, but not participants or assessors. The trial design complies to the Standard Protocol Items: Recommendations for Interventional Trials (SPIRIT) [15] and Consolidated Standards of Reporting Trials (CONSORT) [16] guidelines. An outline of the trial is found in the study flowchart (Fig. 1) and the SPIRIT figure (Fig. 2). The SPIRIT checklist is provided as a supplemental online material (Additional file 1).

**Fig. 1 Fig1:**
[figure not shown]
Study flowchart

**Fig. 2 Fig2:**
[figure not shown]
Schedule of enrolment, interventions, and assessments. Complications in the surgical group will also be assessed at suture removal 2 weeks postoperatively

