### Interventions

#### Treatment arm 1: PIP denervation

Surgical PIP-denervation is performed under local anesthesia (blood-less field with finger-ring or wide-awake local anesthesia no tourniquet (WALANT) according to the surgeon’s preference). A volar approach to the PIP joint is used and a 360-degree denervation is performed as described by Jiménez et al. [9]. The skin is closed by resorbable or non-resorbable sutures depending on the surgeons’ preferences. A soft dressing is applied and removed by the participant after 5–7 days. At 2 weeks postoperatively, a nurse removes non-resorbable sutures and examines the wound for signs of infection or stiffness. Unlimited active motion of the operated joint is encouraged immediately after surgery as tolerated by the participant. No formal hand therapy protocol is used, and participants do not receive any specific conservative treatment (orthoses, education, exercise) after surgery. However, if the finger is considerably stiff or swollen at suture removal, the participant is referred to the hand rehabilitation unit to get standard treatment for postoperative finger stiffness. The need for additional rehabilitation sessions is documented in the study notes.

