**Fig. 4 Fig4:**
[figure not shown]
Strength-promoting exercises

The unloaded active motion exercises (Fig. 3) promote isolated flexion/extension of PIP (Fig. 3c), global flexion/extension of the finger (Fig. 3a, b), and opposition to thumb (Fig. 3d). The participant is encouraged to hold for 3–5 s at end position.At study start: one face-to-face rehab session + information booklet including exercises to improve function and strength and reduce pain2–4 weeks after study start: one 30-min rehab session, face-to-face or video (follow-up, modification of exercises if the participant is unable to perform all exercises due to pain or other problems)3 months after study start: one 30-min rehab session, face-to-face (follow-up, modification of exercises if needed)4–5 months after study start: one optional rehab session if needed, face-to-face or video (follow-up, modification of exercises if needed)6 months after study start: one 30-min rehab session, face-to-face (follow-up, modification of exercises if needed)

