#### Complications to treatment

All suspected complications to treatment will be recorded at the follow-up visits. Specifically, the presence of superficial or deep wound infections or loss of sensation will be recorded. S2PD and Mini Sollerman will be measured preoperatively, 3 and 6 months postoperatively to evaluate any differences in sensation before versus after treatment.

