#### Failure

A hand surgeon performs clinical evaluations of all patients 3, 6, and 12 months after inclusion. The need for additional treatments is discussed at these appointments based on the patient’s symptoms and wishes. Failure of treatment is defined as the need for further surgery. The reason for additional surgery is noted. The date when a participant is enrolled on the waiting list for additional surgery is recorded, and the survival in months will be determined.

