### Withdrawal and safety

In accordance with the ethical permit, participants may withdraw from the trial at any time without giving a reason for doing so and without any negative consequences for their future treatment. PIP denervation has a reported low frequency of complications compared to other surgical options for PIP OA. The most reported complication is transient paresthesia [11]. All surgical procedures induce a low risk of infection. Other than that, the participants are not exposed to any risks. All expected and unexpected complications to treatment are managed at the Department for Hand Surgery at Södersjukhuset. The presence of complications is assessed at the follow-up visits and interim analyses are performed after the inclusion of 20 and 40 participants to assess the frequency of complications. Participants are also provided with contact information to the Department of Hand Surgery and the research team, should any spontaneous adverse event occur. If a high frequency of unexpected complications is noted, the primary investigator will consider early termination of the study. Research participants are covered by Swedish patient insurance (LÖF).

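### Early complications have a scheduled check at 2 weeks in the surgical arm only; recording them at the exercise arm's existing 2–4 week session would even this out cheaply (minor)

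*Protocol article*

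**What the plan says.** Complications are listed among the secondary outcomes (Abstract, Methods). The general rule covers both arms: "All suspected complications to treatment will be recorded at the follow-up visits" (Complications to treatment). The next sentence names particular events: "Specifically, the presence of superficial or deep wound infections or loss of sensation will be recorded". The visits common to both arms are set under Failure: "A hand surgeon performs clinical evaluations of all patients 3, 6, and 12 months after inclusion".

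The surgical arm has one further assessment. The Fig. 2 caption says "Complications in the surgical group will also be assessed at suture removal 2 weeks postoperatively", and Treatment arm 1: PIP denervation says that at this visit "a nurse removes non-resorbable sutures and examines the wound for signs of infection or stiffness". A finger that is markedly stiff or swollen at that point leads to referral, and the need for extra rehabilitation sessions is documented.

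The exercise arm has a rehabilitation session 2–4 weeks after study start, in person or by video (session list in the Exercise section, printed under Fig. 4). Its stated content includes "modification of exercises if the participant is unable to perform all exercises due to pain or other problems". No recording of complications is mentioned for it.

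Withdrawal and safety mentions transient paresthesia and infection, and continues: "Other than that, the participants are not exposed to any risks". It also gives all participants contact details "should any spontaneous adverse event occur".

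Data analyses assigns chi-square tests to categorical between-arm data and the Holm-Bonferroni method to secondary outcomes. It makes no exception for complications.

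**The concern.** Counts of harms can be compared between arms only if the arms are looked at equally often and for the same things. Here one arm has an early scheduled look and the other does not, although a contact with a therapist falls at about the same time.

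The difference matters for a particular kind of event: one that either treatment could produce, that is present in the first weeks, and that has resolved or been forgotten by 3 months. Stiffness and swelling are examples that the surgical 2-week visit is described as picking up. Sensory change is another, because loss of sensation is among the named complications. In the exercise arm such an event would have to be volunteered by the participant or recalled at 3 months.

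No exercise-type event is named for recording, and assessors know the allocation (Study design). What counts as a suspected complication of exercise is therefore left to judgement. A difference between arms that arose partly from the extra look could be read as an effect of treatment.

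**Working it through.** **The plan's own figures.** The protocol states no number for this point. For completeness, the stated sample size reproduces: a difference of 20 with SD 30, two-sided 0.05 (sidedness assumed) and 80% power needs 36.3 per arm by the two-sample t-test, rounded up to 37, with 80.8% power at 37. Nothing below affects it.

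**Scheduled complication assessments, side by side.**

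| Time | Denervation | Education and exercise |
|---|---|---|
| 2 weeks after surgery | Yes (Fig. 2 caption; Treatment arm 1) | – |
| 2–4 weeks after study start | – | Session held; complication recording not stated |
| 3, 6, 12 months | Yes | Yes |
| Total stated | 4 | 3 |

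**When this biases a comparison.** Consider only event types possible in both arms, with the same true rate p and the same time course in each. Let a be the share present at 2 weeks but gone and unreported by 3 months. Let b be the share that start after 2 weeks and are also gone and unreported by 3 months.

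- Surgical arm records p(1 − b).
- Exercise arm records p(1 − a − b).
- Spurious difference = p × a.

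Events in share b are lost in both arms and create no difference. For example, with p = 14%, a = 25% and b = 25%, the arms record 14 × 0.75 = 10.5% and 14 × 0.50 = 7.0%, a difference of 3.5 points. Wound infection is outside this calculation, because exercise cannot cause it.

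**Illustration.** Inputs: 45 per arm (Sample size) and p = 14%. The Background cites 14% for denervation, mainly transient paresthesia. Using it for the exercise arm, and for shared event types, is an assumption. So are the detected shares d. The surgical arm is taken to detect everything (b = 0), so d = 1 − a and, for a given d, the differences are upper bounds. The expected count in the surgical arm is 45 × 0.14 = 6.3; in the exercise arm it is 6.3 × d; the difference is 14 × (1 − d). The last column comes from exact binomial enumeration of the uncorrected two-sided chi-square test at 0.05, without Holm-Bonferroni adjustment.

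| d | Expected count, surgery | Expected count, exercise | Difference (points) | Chi-square rejects |
|---|---|---|---|---|
| 100% | 6.3 | 6.3 | 0 | 5.5% |
| 75% | 6.3 | 4.7 | 3.5 | 8.7% |
| 50% | 6.3 | 3.2 | 7.0 | 20.7% |
| 25% | 6.3 | 1.6 | 10.5 | 47.3% |

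At d = 50%, a true rate of 7% gives a difference of 3.5 points and 11.5% rejection; a true rate of 28% gives 14.0 points and 38.7%. The protocol supplies neither the exercise-arm rate nor a, so these figures show how the mechanism works and do not estimate the bias.

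**The case against.** The strongest reply is that the protocol already collects harms in both arms. The recording rule is not limited to surgery, the named events add to that rule without replacing it, a surgeon sees every participant at 3, 6 and 12 months, and everyone has a route for spontaneous reports. Pain, stiffness, numbness, range of motion and sensory tests are also measured on a common schedule. This stands. A reader might infer that harms of exercise go largely uncounted, and the text does not support that.

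Second, the 2-week visit is centred on the wound. An infection found there is a true surgical harm and is correctly counted. A reader might take every complication found at 2 weeks as bias, which would be wrong. The reply does not cover stiffness, swelling or sensory change, which are not confined to wounds.

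Third, no complication-specific between-arm test is written. The comparison is inferred from the outcome list and the general chi-square sentence, while the safety text speaks of complication frequency and of sensation before versus after treatment. That is fair, and it is why the point concerns any such comparison. Likewise, the Discussion takes surgical risk as a premise; it does not say that an observed difference in complications will be weighed.

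Fourth, the article does not say that problems at the 2–4 week session go unrecorded, and a form may exist in the full protocol, which is not shown. This is possible. However, the Fig. 2 caption singles out the surgical group for an early assessment, so if both arms are meant, the text should say so.

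**Conclusion.** The point holds as a minor one. The protocol states an early complication assessment for the surgical arm and none before 3 months for the exercise arm, although a suitable contact exists. For early, transient events possible in both arms, this can tilt a between-arm complication comparison against denervation.

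That the tilt will occur, or be large, is not shown. It needs shared-type events that are visible at 2 weeks and neither reported nor remembered by 3 months, and the document gives no rate for these. The illustrative 3.5 to 10.5 points rest on an assumed 14% exercise-arm rate, assumed detection of 75% down to 25%, and complete detection after surgery. The primary outcome and the sample size are not touched.

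**What to change.** In Complications to treatment and in Fig. 2:

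- State that complications are recorded at the exercise arm's existing 2–4 week session, with the same questions as the surgical 2-week check.
- Use one list of event types possible in both arms: stiffness, swelling, sensory change and increased pain, each defined identically in the two arms.
- Limit any between-arm comparison of complications to that shared list.
- Report wound-specific events (infection) descriptively for the surgical arm, and exercise-specific events (exercises modified or stopped because of pain) descriptively for the exercise arm. Neither has a counterpart in the other arm.
- Reconcile the sentence in Withdrawal and safety that excludes any further risk with the session text that foresees pain or other problems.

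The cost is one short form at a contact that already takes place, a wording change and a few more recorded events. The timing matches only approximately: 2 weeks after surgery against 2–4 weeks after study start, the latter possibly by video. Recruitment is expected to run until 2027, so the change could still serve later participants. It should start on the same date in both arms, and participants past that point can be compared on the 3-, 6- and 12-month records alone.

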### Study setting

The study is conducted at the Department of Hand Surgery, Södersjukhuset, Stockholm, Sweden. The Department of Hand Surgery at Södersjukhuset is an accredited hand trauma and replantation center and the secondary referral center for hand surgery in the Stockholm, Södermanland, and Gotland regions, serving a population of approximately 2.8 million inhabitants (SCB Statistical database).

### Eligibility criteria

All eligible participants diagnosed with painful PIP joint OA at the Department of Hand Surgery at Södersjukhuset, Stockholm, are asked to participate in the study. One joint is included and in cases of several affected PIP joints the most symptomatic joint, according to the patient, is included.

Participants are selected based on the following eligibility criteria.

Inclusion criteria:

Age ≥ 18 yearsChronic (≥ 6 months) painful idiopathic or posttraumatic OA in the PIP jointRadiological signs of OA on posteroanterior and lateral radiographs assessed by the Kellgren–Lawrence classification (grades II–IV) [17]Any clinical sign of PIP joint OA: pain at palpation, pain during provocation, bony enlargement, or soft tissue swelling

Exclusion criteria:Rheumatoid arthritis or other chronic inflammatory arthritis. History of psoriasis affecting hand joints, gout, or pseudogout of the handOngoing infection in the hand or wristInability to co-operate with the follow-up protocol (language difficulties, severe psychiatric disorder, cognitive impairment, drug addiction)Systemic or Intra-articular glucocorticoids, intraarticular platelet-rich plasma, or hyaluronic acid injections in the affected joint within 3 months before enrollment

### Randomization, allocation, and blinding

All hand surgeons (> 20) working at the Department of Hand Surgery at Södersjukhuset may enroll participants. The hand surgeon in charge of the participant’s treatment collects informed consent. On the day of enrollment, a dedicated research nurse randomly assigns participants (1:1) to one of the treatment arms using sealed, unnumbered envelopes. A block randomization scheme with a fixed block size of 10 is used. The envelopes containing the allocation slips are prepared and mixed by the primary investigator. Participants are stratified according to sex, since idiopathic OA may be more common in women and men are more likely to have posttraumatic OA than women [18]. Blinding of participants and assessors is considered unfeasible due to a scar on an operated finger. Data analysts are blinded to treatment allocation (anonymized data sheets, with treatment arms coded as A or B by an external part before analyses). Participants in the non-operative treatment group are offered denervation surgery after the study’s primary endpoint (12 months). Cross-over during the study period is not allowed.

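### Unnumbered, hand-mixed envelopes prepared inside the trial team, with one fixed and published block size, leave the allocation order unverifiable and, for a well-placed observer, partly predictable

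*Protocol article*

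**What the plan says.** All the relevant features are stated in the protocol article, mainly under Randomization, allocation, and blinding.

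- Assignment: "a dedicated research nurse randomly assigns participants (1:1) to one of the treatment arms using sealed, unnumbered envelopes", on the day of enrolment.
- Blocks: "A block randomization scheme with a fixed block size of 10 is used".
- Preparation: "The envelopes containing the allocation slips are prepared and mixed by the primary investigator".
- Strata: "Participants are stratified according to sex".
- Recruiters: "All hand surgeons (> 20) working at the Department of Hand Surgery at Södersjukhuset may enroll participants", and "The hand surgeon in charge of the participant’s treatment collects informed consent".
- Blinding (Study design): "Data analysts are blinded, but not participants or assessors".

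Study setting names a single department. Trial status gives a start in September 2023 and an expected end of recruitment in 2027. The article appeared in August 2024, so the block size became public during recruitment. The same randomisation section already gives an external party the task of coding the arms A and B before analysis.

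**The concern.** Concealment rests on two conditions. Nobody involved in entry should be able to learn the next allocation, and it should be possible to show afterwards that allocations followed a random order fixed in advance. The stated arrangement weakens both.

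Verification is the more serious weakness. An unnumbered envelope has no place in a sequence. Slips mixed by hand leave no list to compare with, and they are made up within the trial team.

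Predictability comes second. With a constant, disclosed block size and treatment visible to participants and clinical staff, anyone who keeps a tally within a sex stratum can work out the end of a block. The surgeon who takes consent is also the treating surgeon, so a leaked expectation could affect who is entered and when. Blinding the analysts gives no protection at that stage. The Data analyses section plans no adjusted analyses, so even a measured baseline imbalance produced this way would stay in the primary comparison.

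**Working it through.** The protocol states no figure for predictability, so there is none to reproduce. Sample size is not affected by this point.

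**Inputs.** Block of 10, 1:1, hence 5 + 5 slips (Randomization, allocation, and blinding). Total 90 (Sample size). Two sex strata. More than 20 possible recruiters.

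**1. Allocations known with certainty, for an observer who has seen every earlier allocation in the stratum.** The last k allocations of a block are all determined when they belong to the same arm:

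P(last k the same) = 2 × C(10 − k, 5) / C(10, 5), with C(10, 5) = 252.

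| k | Calculation | Probability |
|---|---|---|
| 1 | 2 × 126/252 | 1.000 |
| 2 | 2 × 56/252 | 0.444 |
| 3 | 2 × 21/252 | 0.167 |
| 4 | 2 × 6/252 | 0.048 |
| 5 | 2 × 1/252 | 0.008 |

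The sum is 1.67 per block, which agrees with 2m/(m + 1) = 10/6 for m = 5. Nine completed blocks give 9 × 1.67 = 15 of 90. With two sex strata and part-filled final blocks, simulation gives about 13.7, assuming 70–90% women (the protocol gives no expected sex ratio). Fifteen is therefore an upper figure.

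**2. Correct guesses by the same observer, always naming the arm that is behind.**

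m + 0.5 × (2^10 / C(10, 5) − 1) = 5 + 0.5 × (1024/252 − 1) = 5 + 0.5 × 3.063 = 6.53 of 10, or 65.3% against 50% by chance.

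**3. The same guess by a surgeon who knows only their own patients.** Simulated with 5 + 5 blocks and equally active surgeons: about 51% correct with 20 surgeons and 53.5% with 5. Equal activity and no exchange of information are assumptions.

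**4. Other block schemes.** For smaller fixed blocks the certain share is 33.3% (size 4) or 25.0% (size 6), against 16.7% for size 10. With randomly varied sizes, the simulated guess rate is about 65.5% (6/8/10/12) or 67.9% (4/6/8). Varying the size hides where a block ends, but does not lower the overall guess rate.

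**5. What a count can and cannot reveal.** For a pack of ten, envelopes left plus participants randomised must equal ten, and a finished pack must split 5:5. A lost envelope breaks the first equality. Using the ten envelopes in a chosen order, or exchanging two between participants of the same block, leaves both equalities intact. Only a numbered sequence could show it.

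**The case against.** The strongest reply is that the 65% and the 15 of 90 describe an observer whom the protocol does not place at the point of consent. Recruitment is spread over more than 20 surgeons and about four years, and a separate nurse makes the assignment. Eligibility criteria says that every eligible patient is asked. This stands: the figures are a ceiling, and the single-surgeon result of about 51% is close to chance. It does not cover the research nurse, who sees every assignment, or any pooling of information within one department.

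Second, drawing from a shuffled 5 + 5 pack is a valid permuted block, and mixing sealed envelopes leaves their preparer no ordered list to consult. This also stands. A reader might infer that the primary investigator can steer allocation. The article does not say that this person enrols patients or holds the packs during recruitment, and a role in interim review has no bearing on concealment. What remains is that preparation is not independent of the trial team.

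Third, a reader might infer that any irregularity would go unseen. That is too strong, because a missing envelope would show in a count. Selection or swapping within a block would not.

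Fourth, an article condenses, and a log or the opacity of the envelopes may be described elsewhere. Their absence is therefore not counted here. The point rests on features that the article commits to: no numbers, mixing by hand, one fixed size and preparation by the investigator.

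**Conclusion.** The point holds as a stated weakness in concealment and, above all, in its verification. Without envelope order or a described reference sequence, the trial could not later demonstrate that allocation within blocks followed a random order, however correct the conduct.

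Predictability is real but bounded. It is 1.67 of 10 allocations certain per completed block, at most about 15 of 90, and 65% correct guesses, all for an observer with full knowledge of the stratum. These figures do not support the reading that enrolling surgeons in general can foresee allocations. Nor is ten a poor size in itself, since smaller fixed blocks are more predictable. The difficulty is a fixed, published size combined with open treatment at one centre. Nothing in the document shows that allocation has been subverted. The weakness should be corrected while recruitment is running, because it cannot be repaired in the analysis.

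**What to change.** From the next participant on, use a computer-generated list stratified by sex, generated and held outside the recruiting team. The external party that already codes the arms is an obvious candidate. Reveal each allocation only once the participant has been registered.

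If envelopes are kept, make them opaque and number them sequentially within each stratum. Write the participant ID and date on each before it is opened, and reconcile used envelopes against the list. For packs already in use, count what remains and check that finished packs split 5:5. This is the only verification still available for them.

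Undisclosed, randomly varied block sizes can be added as a secondary measure. They remove most of the certainty at block ends, but should not be presented as lowering the guess rate.

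The cost is a short amendment, which Trial status says needs permission from the ethical review board, and one new list. Participants already randomised are kept. Abandoning a part-used block can leave the arms slightly less balanced, in the extreme by 5 in each sex stratum.
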